**Methods and analysis:**

An open-label, randomised controlled superiority trial will be conducted in haematology clinics in approximately 10 UK National Health Service (NHS) hospitals. The sample size is 120, randomised 1:1 to intervention and usual care arms. The primary outcome is anti-spike-receptor binding domain (RBD) antibody level at 3 weeks post-SARS-CoV-2 booster vaccination. Secondary outcomes are RBD antibody levels at 12 weeks postbooster vaccination, participant global assessments of disease activity, blood films, full blood count and lactate dehydrogenase levels, impact on quality of life, self-reported adherence with request to temporarily pause or continue BTKi, T cell response against spike protein and relative neutralising antibody titre against SARS-CoV-2 viral variants. Additionally, there will be an investigation of any effects in those given influenza vaccination contemporaneously versus COVID-19 alone.

The primary analysis will be performed on the as randomised groups (‘intention to treat’). The difference between the study arms in anti-spike-RBD antibody level will be estimated using a mixed effects regression model, allowing for repeated measures clustered within participants. The model will be adjusted for randomisation factor (first line or subsequent line of therapy), and prior infection status obtained from prerandomisation antinucleocapsid antibodies as fixed effects.

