### Objectives

Primary: Assess the effectiveness of a 3-week pause in BTKi, rather than continuing treatment as usual, on anti-spike-RBD antibody levels at 3 weeks post-SARS-CoV-2 booster vaccination.

Secondary and exploratory: Assess the effectiveness of a 3-week pause in BTKi treatment rather than continuing treatment as usual, on:

Anti-spike-RBD antibody levels at week 12 after booster vaccination.Neutralising antibody titres at baseline and week 3 after booster vaccination against Wuhan D614G and current variant of concern.Effect on T cell response to SARS-CoV-2 spike protein at 3 weeks postbooster vaccination.Responses to booster vaccination at 3 and 12 weeks after vaccination when influenza vaccination was given at the same time.Biochemical disease activity at weeks 3 and 12 postbooster vaccination.Disease activity changes and their tolerability as reported by participants during the 12 weeks postbooster vaccination.QoL at weeks 3 and 12 after booster vaccination.Self-reported adherence to the allocation.

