#### Secondary outcomes

Levels of anti-spike RBD antibody at 12 weeks PBV.Participant assessments of disease activity: global assessment using a Numeric Rating Scale (NRS) with 1-week recall at baseline, 3 and 12 weeks PBV, current disease activity level and change since baseline, 3 and 12 weeks PBV.Disease flare-up (tumour flare) and actions taken to deal with them at 3 and 12 weeks PBV.Effect on QoL (assessed using European Organisation for Research and Treatment of Cancer -Quality of Life Questionnaire (EORTC-QLQ-CLL17)) at 3 and 12 weeks PBV.Adherence with advice to pause or continue BTKi: self-report at 3 weeks PBV.COVID-19 neutralising titre at baseline and 3 weeks PBV.T cell responses against ancestral Wuhan and the latest variant of concern (B1, B4, B5 and Sanofi) at baseline and 3 weeks PBV.

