### Sample collection and transport

Blood (10 mL) will be collected in a serum activator tube at baseline, week 3 and 12 visits, along with four lithium heparin tubes (10 mL). These samples will be transported to a central laboratory (the Clinical Immunology Service) at the University of Birmingham by courier. The central laboratory will centrifuge the samples on the day of arrival, aliquot in cryovials and stored at −80°C. They will then be placed into dry ice storage until the analyses are undertaken. For participants recruited at two of the recruiting centres (Birmingham and London), 20 participants will be sought to give optional additional blood samples, specifically the same as collected at the baseline, weeks 3 and 12 visits, within 48 hours and at 1 week PBV.

A further 4 mL EDTA blood tube and 4 mL serum separating blood tube will also be taken at the baseline, 3-week and 12-week visits and processed in the local hospital laboratory to measure FBC and a blood film, and LDH levels accordingly.

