The primary objective of the statistical analysis will be to identify if a temporary 3-week pausing of BTKi around the time of vaccination against SARS-CoV-2 increases the anti-spike-RBD antibody at 3 weeks postvaccine compared with continuing BTKi treatment without interruption. The anti-spike-RBD antibody levels will be summarised descriptively at baseline and 3 and 12 weeks post-COVID-19 booster vaccination follow-up. The differences between the study arms will be estimated using a mixed effects regression model, allowing for repeated measures clustered within participants. The model will be adjusted for a randomisation factor (first line or subsequent line of therapy), and prior infection status obtained from prevaccination antinucleocapsid antibodies, as fixed effects. A treatment by time interaction will be included. The model is anticipated to use an unstructured covariance matrix, and maximum likelihood estimation. Data will be log-transformed prior to analysis, as appropriate. The adjusted mean difference between the groups will be presented, together with 95% CI and p values. The regression model will be simplified (eg, linear regression) if the planned model does not converge.

Supplemental analyses will explore the time effect between the last COVID-19 vaccination dose and the dose given in IMPROVE. The effect of non-compliance to the randomised intervention will be explored using per-protocol analyses.

The same model as for the primary outcome will be used to analyse the 12-week PVB anti-spike-RBD antibody outcome. Similar supportive analyses as planned for the primary outcome will be performed for 12 weeks PVB data. Overall, 50% and 90% neutralisation by Wuhan and VOC along with, T cell spike response by subtype (spike for Wuhan and VOC, and nucleocapsid and membrane), will be analysed in a similar manner to anti-spike RBD antibody outcome. Other secondary outcomes will be analysed using generalised linear models for binary and continuous data, as appropriate, with model adjustment as described above.

The number of SAEs will be presented by treatment arm. The proportion of participants with at least one SAE will be compared. Details of the events will be presented, together with information on the timing of the events from randomisation.

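### Continuous harm-side outcomes measured at 3 and 12 weeks are assigned generalised linear models; fitted by visit, these leave week-3 data unused at week 12, and the trial's own mixed model would be a small, free improvement

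*Protocol article*

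**What the plan says.** The statistical analysis text of the protocol article (under Sample size and justification) names two classes of model.

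- **Antibody outcomes:** "The differences between the study arms will be estimated using a mixed effects regression model, allowing for repeated measures clustered within participants". The text adds a treatment-by-time interaction, an unstructured covariance and maximum likelihood. Neutralisation and T cell responses are to be handled in a similar way.
- **Everything else:** "Other secondary outcomes will be analysed using generalised linear models for binary and continuous data, as appropriate, with model adjustment as described above". The adjustment referred to is the covariate set: "The model will be adjusted for a randomisation factor (first line or subsequent line of therapy), and prior infection status obtained from prevaccination antinucleocapsid antibodies," entered as fixed effects.

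The outcomes in the second group include several that are measured repeatedly:

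- Quality of life: "EORTC-QLQ-CLL17)) at 3 and 12 weeks PBV", with a baseline assessment shown in Table 1.
- Disease activity: "global assessment using a Numeric Rating Scale (NRS) with 1-week recall at baseline, 3 and 12 weeks PBV".
- Blood counts and LDH: samples "will also be taken at the baseline, 3-week and 12-week visits and processed in the local hospital laboratory to measure FBC", a blood film and LDH. The abstract counts these as secondary outcomes ("participant global assessments of disease activity, blood films, full blood count and lactate dehydrogenase levels, impact on quality of life"). The Secondary outcomes list does not itemise them, but the Objectives include "Biochemical disease activity at weeks 3 and 12 postbooster vaccination".

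The principal analysis uses participants with available outcome data as randomised. The article plans to describe missing data and defers full detail to a separate statistical analysis plan (SAP), which is not shown.

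**The concern.** The choice of model is the reverse of what the visit schedule suggests. Neutralisation and T cell responses have a single post-baseline visit (week 3), yet they follow the antibody approach. Quality of life, the disease-activity rating, blood counts and LDH have two post-baseline visits, where a repeated-measures likelihood has something to add, yet they get a model class with no within-person term.

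These outcomes carry the risk side of the trial. The end of the Introduction calls quality of life and disease activity key secondary outcomes, and the hypothesis is that response improves without significant worsening of disease control.

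A week-12 model fitted to those with a week-12 value does not use the week-3 value of anyone who then goes missing. If missingness at week 12 depended on the week-3 score differently in the two arms, the week-12 difference would be biased. If poor scorers were lost mainly from the pause arm, the bias would understate harm. A mixed model that includes both visits removes this when dropout depends only on observed values.

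**Working it through.** **Inputs from the article.** 120 randomised 1:1, so 60 per arm; 15% missing data allowed for; visits at baseline, 3 and 12 weeks.

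**The plan's own figure.** Effect 0.65 SD, 90% power, two-sided 5%. Normal formula: 2 × (1.960 + 1.282)² / 0.65² = 49.7, so 50 per arm. The t-based version gives 50.72, so 51 per arm and 102 in total. 102 / 0.85 = 120. Both stated numbers reproduce. They concern the primary outcome and do not change here.

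**Assumptions (not in the documents).** Outcomes in SD units with higher meaning worse; between-visit correlation ρ = 0.6, with 0.8 as a variant; probability of missing week 12 logistic in the week-3 score, with slope up to 1.

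**1. Standard errors of a per-visit model.** SE of the week-12 difference = √(2 / (60 × 0.85)) = √(2/51) = 0.198 SD. With missingness unrelated to the scores, simulation gave a mean model SE of 0.198, an empirical SD of 0.199 and type I error of 5.1%. The standard errors are right.

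**2. Bias at week 12.** Without baseline adjustment, the bias in one arm is ρ × δ, where δ is the shift in mean week-3 score among those retained.

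Dropout tied to the week-3 score in the pause arm only (logit = −2 + score):

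- No week-3 effect: δ = −0.137, so bias = 0.6 × −0.137 = −0.08 (simulated −0.074).
- Week-3 effect of 0.5 SD: δ = −0.190, so bias = 0.6 × −0.190 = −0.11 (simulated −0.111). With ρ = 0.8 it is 0.8 × −0.190 = −0.15 (simulated −0.151).

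Milder and stronger settings of this kind span about 0.05 to 0.16 SD. Against the SE of 0.198 that is 0.05/0.198 = 0.25 to 0.16/0.198 = 0.81 of a standard error.

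Same dropout rule in both arms, with a week-3 effect of 0.5 SD: the simulated bias is −0.006 (slope 0.5, ρ = 0.6), −0.025 (slope 1, ρ = 0.6) and −0.035 (slope 1, ρ = 0.8), so at most about 0.04 SD.

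A likelihood estimate that also uses week 3 was within 0.007 SD of the truth in all these runs.

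**3. Precision when missingness is unrelated to the scores.** Variance ratio, mixed model to per-visit model = 1 − ρ² × 0.15. For ρ = 0.6: 1 − 0.36 × 0.15 = 0.946. For ρ = 0.5: 1 − 0.25 × 0.15 = 0.963. The gain is therefore of the order of 3 to 5%.

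**4. Effect of baseline adjustment.** The covariates named do not include the baseline value of the outcome. If it were added, the week-3 to week-12 partial correlation would fall to (0.6 − 0.36) / (1 − 0.36) = 0.375. The precision gain would then be 0.375² × 0.15 = 2%, and the bias would shrink as well.

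**5. Week 3.** Losing week-12 values does not alter a week-3 model, so the visit nearest the pause is largely unaffected.

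**The case against.** The strongest reply is that a generalised linear model at each visit is a standard, valid analysis. The text also says these models are used as appropriate, and visit structure and missing-data sensitivity analyses are ordinary SAP content. This largely stands, and it is why the point is minor. It does not remove the point, because the article names a model class for these outcomes and names a different one for the antibody outcomes. That is a stated choice and not merely an omitted detail.

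A reader might infer more: that the repeated values will be treated as independent, giving standard errors that are too small and an inflated type I error. The documents do not support this. The outcomes are named by visit, which points to an arm difference at each visit. Inflation (about 9 to 14% for correlations of 0.3 to 0.8) needs both visits collapsed into one time-averaged effect with clustering ignored, and no section describes that. Even a pooled fit with a treatment-by-time term held its level in the null runs.

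A reader might also take it as given that participants who feel worse after pausing will be the ones to miss week 12. Nothing in the article says so. The open-label design and the possibility of flare make arm-specific dropout conceivable, no more. The questionnaires can be returned by text link, email or post, so a missed clinic visit need not lose them.

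**Conclusion.** The point holds as a modest improvement to a stated method, not as an error. Per-visit generalised linear models would give valid standard errors and a sound week-3 comparison. At week 12 they forgo information the trial will already hold. The cost is a bias of about 0.05 to 0.16 SD in the less favourable case of dropout driven by the week-3 score in the pause arm only, at most about 0.04 SD if the same rule acts in both arms, and about 3 to 5% in variance if missingness is unrelated to the scores. These sizes rest on an assumed correlation of 0.6 (0.8 as a variant), 60 per arm, roughly the planned rate of missing data, and no adjustment for the baseline value. The mixed model's protection also assumes that dropout depends on observed values only. The unseen SAP may already settle the matter.

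**What to change.** State in the protocol or SAP, before data lock: continuous secondary outcomes measured at both 3 and 12 weeks (EORTC-QLQ-CLL17 scales, disease-activity rating, haemoglobin, platelets, lymphocytes, LDH) will be analysed with the primary outcome's mixed model, with treatment-by-time interaction and unstructured covariance, log-transformed where skewed (for example LDH and lymphocyte count), reporting the arm difference at each visit. Generalised linear models can remain for the binary outcomes. A switch to ordinary generalised estimating equations would not in general remove bias from dropout that depends on the week-3 value, so it is not proposed.

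The cost is one sentence. The model is already planned for the primary outcome; no new data are needed and the sample size does not change.

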### Timing of analysis

The final unblinded (to the study’s non-statistician investigators) statistical analysis will take place after all follow-up has been completed, and sufficient time has been allowed for data collection and cleaning. No formal interim statistical analyses are planned or have been allowed for in the study design.

The trial statisticians will have access to the final dataset. Once the study has been completed and the main finding have been published, the CI will also have access to the final study dataset.

### Patient and public involvement

People with CLL have been involved since inception of the study. Discussion with a small group (six people) of people with CLL confirmed the trial question is of considerable relevance to the CLL community and advised on study design. A Patient and Public Involvement (PPI) representative (LD) is a coapplicant on the grant, a member of the trial management group, and a non-independent member of the TSC. A patient advisory group has been convened and will meet regularly throughout the study. The role of this group is to work with the IMPROVE study team to ensure that the perspective of people living with CLL is considered during the design, conduct and reporting of the research. This will be achieved through the group helping to raise awareness of the study, reviewing documents, inputting on any issues requested by the trial team, and advising on dissemination of the study results to the CLL community.

### Trial oversight and management

The study is sponsored by the University of Birmingham. Day-to-day management of the study and all programming and statistical activities are to be undertaken by the UKCRC Registered Trials Unit-OCTRU at the University of Oxford.

## Discussion

The IMPROVE study is designed to investigate in those with CLL on BTKi therapy for more than 1 year if a 3-week pause in therapy, compared with continuing as usual with BTKi therapy, improves immune responses to COVID-19 booster vaccination. It will assess the quantitative and qualitative humoral response, to ancestral B.1 virus and the latest variant of concern. In addition, cellular immunity will be assessed through T cell responses to ancestral B.1 and omicron variant peptide pools to give a comprehensive assessment of the adapted immune response. It is generally accepted that both binding and neutralising antibodies are correlates of protection against SARS-CoV-2 symptomatic disease, and the contribution of cellular immunity can be important in protection from severe disease among those that are immunocompromised. The study will generate data that will be generalisable for patients taking one of the currently licensed BTKi in the UK and may be applicable to patients taking this therapy for other conditions, where treatment can be safely interrupted. Treatment interruption can be associated with disease flare, and as such, data outcomes of this will be collected over the course of the study in order for the risk/benefit to be assessed to inform future clinical decision-making.

As this study focuses on patients with CLL, we have chosen to use the internationally validated EORTC QLQ-CLL17.^32^ This will identify symptom burden, physical condition/fatigue and worries/fears on health and functioning and allow direct comparison with other published data. Non-blinding of the participants is a potential limitation to the findings, although concordance with study arm will be assessed through the 3-week CRF. Importantly, laboratory personnel will be blinded to the allocation for objective primary and secondary endpoints and, as such, the results should provide clarity for patients and clinicians around any beneficial impact on immunity of pausing BTKi therapy around the time of vaccination. The published results will help to inform national and international treatment guidance.

### Ethics and dissemination

This study has been approved by Leeds East Research Ethics Committee and Health Research Authority (REC Reference:22/YH/0226, IRAS: 319057). It will be publicised to research, clinical and patient communities and other important stakeholders. This paper has been produced using the Standard Protocol Items: Recommendations for Interventional Trials (SPIRIT) reporting guidelines.^36^ Once the study is completed, we aim to publish the study results in a peer-reviewed high-impact journal and present at national and international meetings to ensure maximum impact and rapid dissemination. The study’s PPI partners will advise on the content of all public facing content for dissemination and where else the study’s results should be communicated. There will be no restrictions on the publication of study findings. All authors will be required to meet the International Committee of Medical Journal Editors (ICJME) authorship requirements. Participant-level dataset and statistical code will be made available to bona-fide researchers on request from OCTRU and the CI, once the IMPROVE study findings have been published in full. The full study protocol may be accessed from the National Insitute for Health and Care Research (NIHR) website.

Details of study monitoring arrangements and a history of changes to the protocol is available in online supplemental material.

10.1136/bmjopen-2023-077946.supp1Supplementary data
